### Secondary Outcomes

Secondary outcomes of the study include self-reported questionnaires, resting-state EEG, electrocardiogram (ECG), and quantitative sensory testing (QST), assessed at baseline (T1) and postintervention (T2). Table 1 briefly describes each of the measurement tools used and the time points throughout the study. All tools are reliable and validated for use in individuals with persistent pain and are consistent with previous literature and the Initiative on Methods, Measurement, and Pain Assessment in Clinical Trials (IMMPACT) recommendations for clinical trials in chronic pain [86-90].

**Table 1 table1:** Summary of secondary outcome measures, including descriptions and timeline used.

Outcome domain and constructs		Brief description of measurement tools		Measurement time points
**Pain**				
	Pain severity and interference [91,92]	The Brief Pain Inventory (BPI)–Short Form will be used to measure pain severity (0=no pain, 10=worst pain possible) and interference (0=does not interfere, 10=completely interfere) over the past 24 hours, past week, and past 4 weeks at T1 and T2. At each training session, a single-item BPI will measure pain severity and interference over the past 24 hours.	Full BPI: T1 and T2; Single-item BPI: every training session	
	Pain unpleasantness [93]	Measured using an 11-point numeric rating scale from 0 (not at all unpleasant) to 10 (most unpleasant imaginable) for the past 24 hours and past week at T1 and T2. At each training session, unpleasantness over the past 24 hours will be measured.	Before every session	
	Pain bothersomeness [41,94]	Measured using a 5-point scale ranging from “not at all” to “extremely” over the past 24 hours and past week at T1 and T2. Before every training session, bothersomeness over the past 24 hours will also be measured.	Before every session	
	Pain quality [6,8,66,95-100]	PainDETECT questionnaire: 12 items, each symptom rated on a 5-point scale. Scores <12 indicate nociceptive pain, 13-18 indicate possible neuropathic pain, and ≥19 indicate likely neuropathic pain. Short-form McGill Pain Questionnaire: 22 items, each rated on a 10-point numeric scale to assess pain quality. Leeds Assessment of Neuropathic Symptoms: 5 items with weighted scores ranging from 0 to 24, assessing signs of neuropathic pain. Dolour Neuropathique 4 interview: assess the presence of neuropathic pain symptoms; a cut-off score of 4 or more positive items indicates neuropathic pain.	T_1_ and T_2_	
	Fatigue [101]	Measured using a 10-point numeric rating scale ranging from 0 (no fatigue) to 10 (fatigue as bad as it can be).	T_1_ and T_2_	
**General health and well-being**				
	Depression, anxiety, and stress [102,103]	The Depression, Anxiety, and Stress Scale, containing 21 items. Each item is rated on a scale from 0 (never) to 3 (almost always) to quantitatively measure psychological distress.	T_1_ and T_2_	
	Pain personification [104]	Pain personification questionnaire, containing 11 items scored on a 5-point Likert scale (1=strongly disagree, 5=strongly agree) to measure the participant’s experience of pain as an internal object.	T_1_	
	Intolerance of uncertainty [105,106]	Intolerance of Uncertainty Scale, containing 12 items. Each item is rated on a 5-point Likert scale ranging from 1 (strongly disagree) to 5 (strongly agree).	T_1_	
	Sleep quality and disturbances [107,108]	Pittsburgh Sleep Quality Index, containing 19 items measuring sleep quality and disturbances over a 1-month interval. Total scores range from 0 to 21, with higher scores indicating poorer sleep quality.	T_1_ and T_2_	
**Participant perceptions about intervention and its impact on health and pain**				
	Credibility/expectancy of the intervention [109]	Credibility/Expectancy Questionnaire, containing 6 items to quantify how credible the participant perceived the intervention to be.	T_2_	
	Acceptability of interventions [110]	Numeric rating scale (0-7) assessing acceptability across 7 components of the theoretical framework of acceptability: affective attitude, burden, perceived effectiveness, ethicality, intervention coherence, opportunity costs, and self-efficacy.	T_2_	
	Perceived treatment satisfaction [111]	Single item numeric scale ranging from 0 (not satisfied at all) to 10 (highly satisfied).	T_2_	
	Patient Global impression of change [112,113]	The Patient Global Impression of Change score represents the participant’s perceived change in pain compared with baseline. It is rated on a 7-point scale, from 1 (very much improved) to 7 (very much worse).	T_2_	
	Mental fatigue [114]	Mental fatigue will be assessed using a single-item numeric scale from 0 (I do not feel fatigued at all) to 10 (I feel extremely fatigued).	T_2_	
	Mental strategies [72]	Patients will be asked whether they used any mental strategies during training sessions and if yes, to report which strategies they used.	T_2_	
	Level of motivation [52]	The Current Motivation–Brain Computer Interface will be used at T1. It uses a 7-point Likert scale across 4 components: mastery confidence, fear of incompetence, interest, and challenge related to electroencephalography neurofeedback training. A single-item 11-point numeric scale will be used for motivation before each training session, ranging from 0 (not motivated at all) to 10 (extremely motivated).	T_1_ and before every training session	
	Mood [52,115]	Mood will be measured before every neurofeedback session using a single item from the Brief Mood Introspection Scale, ranging from 0 (very unpleasant) to 10 (very pleasant).	Before every training session	
	Level of engagement with the training [52]	A 10-point numeric scale will be used, ranging from 1 (least engaged) to 10 (highly engaged).	After every training session	

### Electroencephalographic Measures

Resting-state EEG will be recorded (sampled at 256 Hz) using a 21-channel system (Fp1, Fp2, F7, F3, Fz, F4, F8, T7, C3, Cz, C4, T8, P7, P3, Pz, P4, P8, O1, O2, A1, A2; BrainMaster Technologies, Inc) [43]. Raw EEG recordings will be collected for 10 minutes with participants’ eyes closed. To minimize potential artifacts, participants will be instructed to avoid facial movements, head and neck movements, and swallowing. Alertness will be monitored by observing the presence of spindles and slowing of the alpha rhythm in the EEG stream to prevent drowsiness-related increases in theta power during the recording [116].

Each EEG file will be resampled to 128 Hz and bandpass filtered for 0.01-44 Hz in EEGLAB (MATLAB R2020a) [117]. Artifacts such as eye blinks, muscle artifacts, perspiration, and body movements will be filtered out using ICoN software [52,118].

Exact low-resolution brain electromagnetic tomography (eLORETA) software will be used to extract the following EEG variables. First, ROI current density, for which frequency-specific data will be collected by performing a voxel-by-voxel analysis containing 6239 voxels for each of the following frequency bands at the dACC and RIns: infraslow (0.01-0.10 Hz), slow (0.2-1.5 Hz), delta (2-3.5 Hz), theta (4-7.5 Hz), alpha (8-12 Hz), beta (12.5-30 Hz), and gamma (30.5-44 Hz). Comparisons will be made between participants’ pretreatment and posttreatment measures using eLORETA statistical contrast maps. Multiple voxel-by-voxel comparisons in the logarithm of t-ratio with a threshold of *P*≤.05 will be used to compute the cortical 3D distribution of current density [49].

Second, functional connectivity will be assessed using lagged linear connectivity, which is a statistical measure of coherence representing the phase synchronization between ROIs within the brain, as it combines the relationship between the phase and amplitude of the signals [23,24]. This measure reflects the level of communication between the ROIs [90]. Log-transformed lagged linear connectivity will be derived for all possible connections across the 7 frequency bands between the dACC and RIns.

eLORETA is an EEG source localization software that computes current density across the full brain volume [119] to localize cortical brain structures with fewer localization errors for EEG data extraction and analysis [120]. eLORETA has been widely used in previous literature for EEG analysis [121-123].

### Cardiovascular Measures

Heart rate variability (HRV) metrics will be obtained using a Polar V800 heart rate monitor and a Polar H10 Chest Pro Strap [124]. The ECG monitor will be placed below the sternum and secured to ensure a fixed position for the participant. Raw heart rate and R-R (peak-to-peak R wave) interval time series data will be downloaded from the Polar Flow software for further processing and analysis. Kubios HRV Premium (v3.2.0) software will be used to analyze HRV from the R-R interval record exported from the Polar Flow software [125]. The root-mean-square of successive differences between normal heartbeats and stress index (SI) will be extracted for HRV analysis. Root-mean-square of successive differences quantifies the variability between adjacent respiratory rate intervals, demonstrating a lesser susceptibility to influence by the respiratory system and, due to this, is regarded as the most dependable HRV for monitoring vagal response [125,126]. The SI will be calculated using the square root of the Baevsky SI model [127]. Given that the insular cortex and dACC are key regions involved in interoception—integrating internal bodily signals to regulate physiological and emotional states—any changes in sympathetic and parasympathetic activity can be effectively captured through HRV analysis [80,128,129].

### Quantitative Sensory Testing Measures

The following QST measurements will be performed at T1 and T2. All QST measures were included based on previous literature demonstrating variability in these clinical measures among individuals with chronic MSK pain and NP [130-132].

#### Pressure Pain Threshold

A computerized algometer (AlgoMed, Medoc) will be used to measure pressure pain threshold on the dorsal aspect of the nondominant wrist of the participant for 3 trials [133,134]. Two familiarization trials will be performed at the mid-forearm before the formal trials. Pressure will be applied to the test site gradually at a rate of 30 kPa/s for each participant by placing a 1-cm^2^ probe perpendicular to the site until the participant reports that the pressure has become a pain sensation. Participants will be instructed to verbally inform the investigator immediately when they perceive pressure as pain. The average of the 3 tests will be used for analysis [135].

#### Punctate Pain Intensity

Punctate pain intensity will be assessed using a nylon filament (Semmens monofilament 6.65, 300 g) on the nondominant wrist of the participant for 3 trials [134,136]. The nylon monofilament will be applied perpendicular to the site on the nondominant wrist with enough force to bend the filament. Immediately after each trial, participants will report their pain intensity on a 101-point numeric pain rating scale (0 indicating no pain at all and 100 indicating the most intense pain they have ever experienced) [137]. The average across the 3 trials will be calculated.

#### Mechanical Temporal Summation

Mechanical temporal summation (MTS) will be assessed using a nylon filament (Semmens monofilament 6.65, 300 g) on the dorsal aspect of the nondominant wrist of the participant for 3 trials [134]. Participants will be instructed to provide a pain rating on a 101-point numeric pain rating scale. Immediately after this, 10 consecutive contacts with an interstimulus interval of 1 second will be performed, and participants will be asked to provide a pain rating on the 101-point numeric pain rating scale again. MTS will be calculated as the difference between the initial value after the first contact and the highest pain rating after the tenth contact. The average of these 3 trials will then be used in analysis.

#### Vibration Detection Threshold

A tuning fork (64 Hz, 8/8 scale) will be used to test a participant’s ability to detect vibration and will be placed on the dorsal aspect of the nondominant wrist with suprathreshold vibration intensity. It will be held in place until the participant can no longer feel the vibration [134,138,139]. This will be graded on an 8/8 scale, with 8 indicating the highest level of sensitivity to vibration [140]. The vibration detection threshold will be determined using the mean of 3 consecutive tests for each location [141].

#### Medication and Other Treatment Monitoring

Any concurrent treatments will be monitored, including regular general practitioner visits, use of physiotherapists, osteopaths, chiropractors, and self-management as well as current medications. Any medications that participants are taking regularly will be recorded at the baseline assessment. Changes in dosage, as well as the frequency of use of pain-relief medications during the study period, will be noted at each session.

### Analysis

#### Primary Outcomes

Participant demographics, feasibility, acceptability, credibility, and safety data over the course of the study will be summarized descriptively [142]. Mean (SD) or median (IQR) when distributional assumptions are not met and CI (75% and 95%) of the clinical and quantitative outcome measures for the participants will be derived using GraphPad Prism software [143]. Feasibility will be assessed against prespecified progression criteria: ≥50% of eligible participants consenting, recruitment meeting target within the planned window (~6 participants in 4 months), retention ≥80% at postintervention, adherence ≥75% of scheduled sessions, data completeness ≥85%, and mean acceptability ≥70%. Each metric will be reported as a point estimate with 95% CIs, and progression will be discussed in light of these thresholds [60,144,145].

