**Results:**

This study has received approval from the Health and Disability Ethics Committee and is registered with the Australian New Zealand Clinical Trials Registry. Participant recruitment began in April 2025 and is ongoing. As of October 2025, data collection has been completed, with a total of 5 participants enrolled, all of whom have completed the study to date. We expect to complete the study in March 2026. This study will generate data on feasibility, safety, acceptability, and preliminary data to inform a fully powered effectiveness clinical trial.

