Therefore, this study aims, for the first time, to explore the potential of downregulating the ISF activity of both the RIns and dACC using a novel ISF EEG-NF protocol in individuals with NP-like symptoms associated with chronic MSK pain conditions. Given the novelty of the proposed ISF EEG-NF training protocol, pilot testing of the protocol and assessment of feasibility and safety are necessary. The primary objectives of this study are (1) to pilot test and investigate the feasibility of the EEG-NF program, and (2) to investigate the safety of the ISF EEG-NF training. The secondary objectives are (1) to estimate the variability of the outcome measures for informing the sample size of a fully powered clinical trial, (2) to explore the immediate and short-term trends of the effects of the targeted ISF EEG-NF training on pain measures, and (3) to explore the changes in EEG current density activity at the targeted cortical regions (dACC and RIns) and the functional connectivity between these regions following ISF EEG-NF training.

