### Recruitment

Convenience sampling will be used to recruit participants from the wider Dunedin community. Periodic advertising in community newspapers and social media will be carried out. Posters will be placed throughout the local community to advertise the study for participant recruitment.

Interested participants will undergo eligibility screening by telephone or through a secure online survey using Research Electronic Data Capture (REDCap; Vanderbilt University) web application [62]. As this is a pilot-feasibility study, a formal power-based sample size calculation was not undertaken. Instead, the sample size was determined as 6-12 participants over a 4-month recruitment period, in accordance with recommendations for feasibility studies and previous literature, ensuring adequacy to evaluate safety and feasibility outcomes while also permitting exploratory analyses [63].

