## Results

This study was funded in January 2025. As of October 2025, data collection has been completed, with a total of 5 participants enrolled. The target sample size for the study was 12 participants. Data analysis will commence in November 2025 and will continue for 3 months following the completion of data collection. The results of the study are expected to be published once data collection and analysis are complete in late 2026 or early 2027. Any deviations from the protocol, regardless of the reason, will be documented in the Australian New Zealand Clinical Trials Registry and reported in the final publication.

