### Conclusions

The data and findings of this study will aid in designing future fully powered clinical trials to further evaluate the efficacy of this novel ISF EEG-NF training for NP management. Additionally, the foundational data from this pilot open-label feasibility trial will provide the necessary information to enable future studies to perform power calculations for designing upcoming trials.

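### The summary rule does not guarantee an SD for outcomes that fail the distribution check, although the pilot is meant to supply variability for sizing the next trial

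*Protocol article*

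**What the plan says.** Protocol article, Analysis, Primary Outcomes: the summary is "Mean (SD) or median (IQR) when distributional assumptions are not met and CI (75% and 95%) of the clinical and quantitative outcome measures". The mean (SD) and the median (IQR) are alternatives, and the distributional assumptions decide between them. The same sentence says "CI (75% and 95%) of the clinical and quantitative outcome measures for the participants will be derived using GraphPad Prism software". It names neither the parameter (mean or median) nor the interval method.

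Introduction, secondary objective 1: "to estimate the variability of the outcome measures for informing the sample size of a fully powered clinical trial". The Conclusions section adds that the data "will provide the necessary information to enable future studies to perform power calculations for designing upcoming trials", and the abstract's conclusions also tie the results to the sample size of a randomised trial.

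Analysis, Secondary Outcomes: the pre-post comparison is chosen according to normality. Changes in clinical ratings are analysed with effect sizes, paired t tests and Wilcoxon signed-rank tests.

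Sample size: under Recruitment, "the sample size was determined as 6-12 participants over a 4-month recruitment period". The Results section says "As of October 2025, data collection has been completed, with a total of 5 participants enrolled". The abstract's results repeat this but also state "Participant recruitment began in April 2025 and is ongoing".

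**The concern.** The summary rule and the secondary objective pull in different directions. An IQR describes spread, but the usual sample-size formula for a continuous endpoint takes an SD, preferably the SD of change as well. Under the rule, whether an outcome yields that figure depends on a distribution check applied to a handful of participants. Candidate endpoints for the next trial could then be reported on different footings, some with an SD and some without.

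There is a less visible effect. In a small sample from a skewed distribution, the check tends to fail when an extreme value is present, which is also when the sample variance is large. The SDs that pass are therefore a selected, low set. Required sample size is proportional to variance, so a planner who uses them would tend to under-size the next trial.

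A secondary question is whether a 95% interval can be attained for a median with as few as 5 participants.

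**Working it through.** The plan gives no power, alpha or computed sample size to reproduce; 6-12 rests on recommendations and literature.

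**1. Does any section guarantee an SD for every outcome?**
- Analysis, Primary Outcomes: the SD is given only when the assumptions are met.
- Analysis, Secondary Outcomes: a paired t test implies an SD of change, but that commitment concerns clinical ratings. It does not clearly extend to heart rate variability, sensory testing or EEG current density. The comparison for all secondary outcomes is again selected by normality.
- Introduction and Conclusions: they state the purpose but fix no statistic.

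So no section guarantees it.

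**2. What does the gate do?** The article names no check and no distributions, so these are assumptions: Shapiro-Wilk at 5%; lognormal outcomes with log-SD 0.5 or 1; sample sizes 5 (reported enrolment) and 12 (stated target). The simulation draws samples, applies the check, and divides the mean sample variance among passing samples by the true variance, exp(s²)(exp(s²) − 1) for log-SD s.

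| n | log-SD | SD dropped | mean variance / true variance, SD kept | same ratio, SD always reported |
|---|---|---|---|---|
| 5 | 0.5 | about 10% | about 0.88 | about 1.0 |
| 5 | 1 | about 24% | about 0.48 | about 1.0 |
| 12 | 0.5 | about 30% | about 0.76 | about 1.0 |
| 12 | 1 | about 71% | about 0.26 | about 1.0 |

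Repeat runs at n=5 gave 0.87 to 0.90 (log-SD 0.5) and 0.46 to 0.48 (log-SD 1).

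The rows can be checked by averaging over kept and dropped samples. At n=5 and log-SD 0.5, the dropped samples must average (1.0 − 0.90 × 0.88) / 0.10 = 2.1 times the true variance. At log-SD 1 they must average (1.0 − 0.76 × 0.48) / 0.24 = 2.6 times. The gate removes the high-variance samples.

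For a fixed target difference, N is proportional to variance. A trial sized from the retained raw-scale SDs would therefore average about 88% or 48% of the required N at n=5, and about 76% or 26% at n=12.

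**3. Interval for a median.** The exact distribution-free interval from the k-th smallest to the k-th largest value covers 1 − 2 × Σ_{i<k} C(n,i) / 2^n.
- n=5, minimum to maximum: 1 − 2/32 = 93.75%.
- n=5, second to fourth value: 1 − 2 × (1 + 5)/32 = 62.5%.
- n=6, minimum to maximum: 1 − 2/64 = 96.9%.
- n=12, third to tenth value: 1 − 2 × (1 + 12 + 66)/4096 = 96.1%.

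The signed-rank interval has the same ceiling at n=5 (1 − 2/32 = 93.75%). At n=5, then, no exact distribution-free 95% interval is available, and the 75% level can be met only by the same minimum-to-maximum range.

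**The case against.** **Most skewed outcomes would keep their SD.** A reader might infer that skewed outcomes simply go without an SD. The documents do not support that. Under the assumed check at n=5, about 76% to 90% of such samples pass and keep it, and the article does not say which outcomes are skewed. What remains is that the SD is not guaranteed, and that those retained are selected low.

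**Variability is not the same word as SD, and part of the need is met elsewhere.** An IQR is a measure of variability, and the paired t tests and effect sizes for clinical ratings, which are plausible endpoints for the next trial, can yield an SD of change. This stands for those ratings, subject to the normality condition in the same section. It does not cover every outcome.

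**Converting the IQR back to an SD.** A reader might try to size the harm by dividing the IQR by 1.349 under normality. That is the wrong case: the IQR replaces the SD mainly when data do not look normal, and the article proposes no such conversion. No weight is placed on it.

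**Reporting the SD does not make it precise or free of skew effects.** In samples that fail the check at n=5, the sample SD averages 1.27 and 1.23 times the true SD (log-SD 0.5 and 1). Even under normality, the 95% interval for an SD from 5 values runs from 0.60 to 2.87 times the estimate. Both points are fair. Unconditional reporting removes the selection, not the imprecision. For strongly skewed measures a planner might also prefer the log scale, which the article specifies for connectivity: "Log-transformed lagged linear connectivity will be derived for all possible connections across the 7 frequency bands between the dACC and RIns".

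**Median intervals.** A reader might infer that the plan promises a 95% interval for a median that cannot be constructed. The text promises intervals for the outcome measures without naming a parameter. The planned minimum of 6 already allows 96.9%, and the article is inconsistent on whether 5 is final. The limit concerns exact distribution-free intervals only.

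**This may be analysis-plan detail.** The interval method and table layout commonly are. The either-or rule is different, because the article states it and it fits poorly with a stated objective.

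**Conclusion.** The concern holds in a limited form. The stated rule puts median (IQR) in place of mean (SD) whenever the check fails, and nothing else in the article guarantees an SD for every outcome, although secondary objective 1 and the conclusions rely on this pilot to size the next trial.

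The size of the effect depends on the assumed lognormal shapes and the assumed Shapiro-Wilk check at 5%; neither comes from the article. Less skewed outcomes or a different check would change it. The downward selection arises because the SD is withheld when the check fails, and it disappears when the SD is always reported.

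The median-interval point is secondary and doubly conditional: it matters only if the final sample stays at 5 and the interval is for a median. It is not a fault of the planned range of 6-12.

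**What to change.** Change the either-or rule to a both rule. For every outcome measured at T1 and T2, report the mean, the SD at each visit and the SD of change, regardless of any distribution check, and add median (IQR) where useful.

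Name the parameter to which the 75% and 95% intervals refer. If the final sample is 5 and a median is used, label the minimum-to-maximum interval with its attained 93.75% coverage, or give the t-interval of the mean change instead. Reconcile the statements on whether recruitment is ongoing or data collection is complete, since the sample size decides whether this applies.

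The cost is one sentence of analysis wording and a few table columns. No new data are needed.
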